### Assessments

Primary outcome measures are symptoms of depression and anxiety. Secondary outcome measures are drop-out from the intervention, quality of life, and economic costs. Other secondary outcome measures that may predict outcome are also studied, e.g. client satisfaction and problem-solving skills. Measures are taken at baseline (pre-test), directly after the intervention (post-test, five weeks after baseline), three months later, and 12 months later. All measurements are self report measures and will be administered through the internet.

### Instruments

#### Primary outcomes

##### Depressive symptoms

###### CES-D

The Dutch version of the Center for Epidemiological Studies Depression scale (CES-D [26] has 20 self-rated items; each scored 0–3; total score range is 0–60. Among different populations, the paper-pencil CES-D has acceptable psychometric properties with a cut-off score of 16 (sensitivity: 0.84–1.00, specificity: 0.69–0.90 [27-29]). The Internet CES-D is also reliable and valid with a cut-off score of 22 (Cronbach's alpha: 0.90; AUC: 0.84; sensitivity: 0.94; specificity: 0.62) in an adult population [30].

###### PHQ-9

The nine-item mood module of the Patient Health Questionnaire (PHQ-9 [31]) is used to screen and to diagnose patients with depressive disorders. The 9 items are each scored 0–3, total score range is 0–27. In a review of Wittkampf et al. [32], a sensitivity of 0.77 (0.71–0.84) and a specificity of 0.94 (0.90–0.97) was found for the PHQ-9.

### Anxiety symptoms

#### HADS

The 7-item anxiety subscale (Dutch version) of the Hospital Anxiety and Depression Scale (HADS [33] is used for identifying anxiety symptoms. Cronbach's alpha ranged between 0.81 to 0.84, in different normal and clinical Dutch samples [34]. Item-responses are on a 0 to 3 scale, total score range is 0–21 with higher scores indicating more anxiety.

#### BAI

The 21-item Beck Anxiety Inventory (BAI [35]) assesses anxiety, with a focus on somatic symptoms. Item responses are on a 0 to 3 scale, total score ranges from 0 to 63, with higher scores indicating more anxiety. The BAI has high internal consistency and demonstrated good convergent and divergent validity [36,37].

### Secondary outcomes

#### Quality of life

The 5-item self-report Euroqol [EQ; 38] measures health-related quality of life and consists of five dimensions (mobility, self-care, main activity, pain and mood), each of which is rated as causing 'no problems', 'some problems', or 'extreme problems'. The EuroQol valuations appear to have good test-retest reliability [39]. Brazier et al. [40] found considerable evidence for the construct validity of the EQ. There was substantial evidence of EQ being less sensitive at the ceiling (i.e. low levels of perceived ill-health) and throughout the range of health states.

#### Health care utilization

A health service uptake and production loss due to illness, which produces economic costs, is measured with the iMTA Questionnaires on Costs Associated with Psychiatric Illness (TiC-P [41]). This structured interview gives an indication of direct and indirect costs of the intervention and consists of two parts: (i) the amount of medical care received by the participants and (ii) work productivity.

#### Working alliance inventory (WAI)

The Working alliance inventory (WAI [42]), measuring work alliance, is a 36-item self-report questionnaire and makes use of Likert response scale from never to always. Good construct validity and good to high internal consistency was found in a study of Horvath and Greenberg [42], its construct validity is supported in other studies in which the WAI was compared to other working alliance instruments [43].

Only the 21 questions which were relevant to our type of study (role of support) will be used, which are: questions 1–3, 5, 6, 8–10, 12, 17–21, 24, 25, 27–29, 32–33. All words regarding "nurse" or "nurse-treatment protocol" will be changed to "coach" and "treatment protocol". This questionnaire will only be administered to those in condition 2, 3 and 4 (with a coach).

#### Client satisfaction

The Dutch version of the Client Satisfaction Questionnaire (CSQ-8 [44,45]) is used to assess global patient satisfaction. De Brey [45] found a high internal consistency (Cronbach's α = 0.91), similar to the original English version (Cronbach's α = 0.93). The 8-item self report questionnaire scale response options are from 1 to 4, total score ranges from 8 to 32.

#### Mastery

The 7-item Mastery Scale [46] ranges from 1 to 5, total scale score 7–35. A high score (internal mastery) indicates that someone has the feeling to be in control of situations. A low score (external mastery) indicates that someone has the feeling that things are out of their control. The questionnaire has good psychometric properties [46].

#### Expectancy

The Credibility/Expectancy Questionnaire of Devilly and Borkovec (CEQ [47] is used to measure expectancy for change and treatment credibility. These two factors have been found to be stable across different populations, with high internal consistency within each factor and very high test-retest reliability [48]. It comprises six questions, four on "thinking" and two on "feeling." On the "thinking" questions, three are rated on a Likert-type scale from 1 to 9 and the fourth is rated from 0 to 100%.

#### Web Screening Questionnaire for common mental disorders (WSQ)

To quickly detect if participants have symptoms of depression or anxiety, we administer the WSQ simple version. Sensitivity of the WSQ ranged from 0.60 to 1.00 while specificity varied between 0.44 and 0.77 [49].

#### Personality disorder

The 8-item Standardized Assessment of Personality Abbreviated Scale (SAPAS [50] Moran et al., 2007) is used to screen for personality disorder. Each item is dichotomously scored (0–1), total score ranges from 0 to 8. A score of 3 on the screening interview correctly identified the presence of DSM-IV personality disorder in 90% of participants. The sensitivity and specificity were 0.94 and 0.85 respectively [50].

#### Motivation

To measure the motivation of participants for self-help therapy, we use three questions of the screening questionnaire (SQ), a quick self-report developed by Marks et al. [51]. Likert-scale response options are used, total score ranges from 0 to 8.

#### Suicidal intentions

To measure suicidal intentions of participants we use one question of the screening questionnaire (SQ), a quick self-report developed by Marks et al. [51]. Likert-scale response options are used, total score ranges from 0 to 3, cut off score is above 3.

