### Inclusion and exclusion criteria

Participants who return the informed consent will be included in the study if they: 1) are 18 years or older; 2) have symptoms of depression and/or anxiety (as defined by scoring above the cut-off of 16 on the Center for Epidemiological Studies Depression scale (CES-D) and eight on the Hospital Anxiety and Depression Scale (HADS); 3) which are not too severe (1 standard deviation above the population mean on the CES-D, cut-off < 39 and/or HADS cut-off <15 [16,17]), 4) have access to a computer with a fast internet connection and 5) have sufficient knowledge of the Dutch language. Excluded are subjects with severe depressive or anxiety disorders (score ≥ 39 on the CES-D; ≥ 15 on HADS), active suicidal plans (≥ 3 SQ suicide) and/or currently under treatment by a mental health specialist. Participants will not be excluded if they are taking prescribed medicine for anxiety or depressive disorders over one month with stable dosage.

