### Recruitment

A total of 500 participants with mild to moderate depression and/or anxiety will be recruited from the general population through banners on internet websites (Google, Dutch internet-sites on mental health issues), as well as local newspapers. All advertisements are in Dutch. In choosing the websites specific attention will be paid to include patients with different ethnic backgrounds and socioeconomic groups. In these banners, a link to a website is given which contains information about the study. Patients can leave their names and email address when interested in the study. More extensive information will then be sent by post, together with an informed consent form and a link by e-mail to the online baseline-questionnaire. Subjects who meet the inclusion criteria (as described above) will be randomized to the different treatment arms and will be notified by email. Subjects who are excluded will be notified by email and advised to contact their GP when their symptoms of depression or anxiety are severe (as determined by the CES-D and HADS). For practical reasons, recruitment will take place in batches of 100 participants.

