#### Support

In condition one, automated standardized emails are sent to subjects with additional information regarding how to make the exercises. There will be no support from a coach.

In condition two, the respondent has the option to contact the coach by email for additional support and in condition three, the coach will actively approach the respondents per email, once per week. This will take 10 to 15 minutes per week; total coaching time is estimated at one to 1.5 hours per respondent [13]. Coaching is only meant to give support in working through the self-help method and not aimed at developing a patient-therapist relation. The participants in condition four receive non-directive support by their coach via email or chat. Coaching will be given by Master level students in clinical psychology. Coaches for condition 2 and 3 will receive a training of approximately six hours given by the first and second author of this article. The training will consist of reading the interventions materials themselves, carrying out assignments, and practicing feedback to each other by e-mail. During the training they will also practice with case material and their feedback will be discussed. The training for condition four, non-directive support, will be given by the first author of this article and consists of carrying out assignments and practicing non-directive conversation skills for approximately four hours.

In all five conditions two automated emails will be send to participants reminding them about when they can fill in the post-test measurement. Based on a recent study of Nordin et al. [Nordin S, Carlbring P, Cuijpers P, & Andersson, G: Expanding the limits of bibliotherapy for panic disorder. Randomized trial of self-help without support but with a clear deadline, submitted], we expect participants to adhere better to the program when they are aware of a deadline, in which their symptoms are surveyed.

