### Sample size

The effects of the intervention on symptoms of depression and anxiety are the primary outcome measures and these are used as starting point for the power calculations. We assume that we want to be able to show differences between interventions and the control conditions with a standardized effect size (Cohen's *d*) of 0.35 [13]. Smaller effect sizes are considered to be not relevant from a clinical point of view. Assuming an alpha of 0.05 and a statistical power (1-Beta) of 0.80 in a one-tailed test, we need 100 respondents in each of the conditions. Overall, we need to recruit 500 respondents in total.

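### The suicide item's cut-off lies outside its own stated range and conflicts with the exclusion rule at score 3

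*Protocol article*

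**What the plan says.** Two places in the protocol article set a threshold for the same item.

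- **Instruments, Suicidal intentions.** The measure is a single question: "To measure suicidal intentions of participants we use one question of the screening questionnaire (SQ"). Its scoring is given as "total score ranges from 0 to 3, cut off score is above 3".
- **Inclusion and exclusion criteria.** Among the grounds for exclusion is "active suicidal plans (≥ 3 SQ suicide").

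The Recruitment section ties randomisation to the eligibility section: "Subjects who meet the inclusion criteria (as described above) will be randomized to the different treatment arms". The Assessments section adds: "All measurements are self report measures and will be administered through the internet". Table 1 lists the SQ only under motivation, at baseline, and gives neither a range nor a cut-off for the suicide item.

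**The concern.** A cut-off set above the top of the scale cannot be reached, so the instrument description taken literally is a screen that never triggers. It also disagrees with the eligibility section at the one score where a decision matters, the most severe answer.

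This is a safety exclusion. It is the only suicide-specific criterion in the article, and it rests on the item score: every measure is an online self-report, and the Discussion names the lack of a diagnostic interview as a limitation. The article describes no clinician check that would catch a mis-scored answer. The Background itself counts the risk of missing people for whom pure self-help is not enough among the arguments against unguided programs. Two of the five conditions have no coach: condition 1, of which the Support section says "There will be no support from a coach", and condition 5, which offers only an information website. If the online screen followed the instrument description, someone giving the highest answer could be randomised to either.

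**Working it through.** **Inputs**

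- Item: one question, stated range 0 to 3 (Suicidal intentions). Possible whole-number scores: {0, 1, 2, 3}.
- Rule A: score > 3 (Suicidal intentions).
- Rule B: score ≥ 3 (Inclusion and exclusion criteria).
- Planned size: "we need 100 respondents in each of the conditions" (Sample size), with five conditions and 500 in total.

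**Step 1. Apply both rules to the stated range**

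| Score | Rule A (> 3) | Rule B (≥ 3) |
|---|---|---|
| 0 | not excluded | not excluded |
| 1 | not excluded | not excluded |
| 2 | not excluded | not excluded |
| 3 | not excluded | excluded |

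Rule A excludes 0 of 4 scores and rule B excludes 1 of 4. They differ at score 3 only.

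**Step 2. Suppose the range is the misprint**

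The article does not show whether the range or the cut-off is wrong. Taking two larger maxima purely as assumptions:

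| Assumed maximum | Rule A excludes | Rule B excludes | Rules differ at |
|---|---|---|---|
| 3 (as stated) | none | 3 | 3 |
| 4 | 4 | 3, 4 | 3 |
| 8 | 4 to 8 | 3 to 8 | 3 |

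With a larger range rule A becomes attainable, but the disagreement at score 3 remains. The impossibility depends on the printed range; the contradiction does not.

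**Step 3. What would follow if rule A were programmed**

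A person with score 3 who met all other criteria would be randomised. With 100 planned in each condition, the chance of allocation to a condition without a coach (1 or 5) is

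(100 + 100) / 500 = 0.40.

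This describes allocation and is not a measure of risk. How many people would be affected cannot be calculated, because no distribution of the item score is given.

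**Step 4. Check the correction**

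With the instrument description changed to ≥ 3 on the range 0 to 3, both sections exclude {3} and agree at every score.

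**The case against.** The strongest reply is that the rule that governs entry is sound. Eligibility is set in the Inclusion and exclusion criteria, Recruitment points back to them, and that threshold can be met on a 0 to 3 item. The instrument description states no exclusion of its own. The article is also loose about cut-offs elsewhere: for the CES-D the eligibility section requires scores above the cut-off of 16, while the instrument section simply gives 16 as the cut-off. A reader who met an unattainable threshold would probably go back to the eligibility section. This stands, and it is why the point is minor.

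Three further objections limit the consequences. The CES-D and HADS upper limits and the exclusion of people under specialist treatment apply at the same screen and may remove some of those concerned. The 40% figure needs the unproven premise that the screen was built from the instrument description. And a coach is not described as a safeguard: in the self-help conditions coaching is confined to help with the method, and in condition 2 contact happens only if the participant asks. These are fair, and the 40% should be read accordingly.

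None of this removes the mismatch. The severity limits are not suicide criteria. The eligibility section writes ≥ where it means at or above, so a reader has no reason to take a cut-off above 3 as including 3. Nor can the threshold be a symbol lost in text extraction, since it is spelled out in words.

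**Conclusion.** The point holds. As printed, the cut-off in the instrument description cannot be met on the item's own range, and it contradicts the eligibility section at score 3. The size is one score out of four, the highest.

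The severity is minor. If the eligibility rule was applied as written, score 3 is excluded and nobody is wrongly admitted. Harm requires the online screen to have been scored from the instrument description, and the article gives no evidence on that either way. There is no effect on sample size, alpha or the analysis.

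The conclusion that no score qualifies assumes the printed range of 0 to 3 is correct. The conclusion that the two sections conflict needs no such assumption.

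**What to change.** 1. Check the item's response range against the source questionnaire.
2. If 0 to 3 is right, change the cut-off under Suicidal intentions to 3 or above, so that it matches the eligibility section.
3. If the range is wrong, correct it and state one confirmed threshold in both sections.
4. Confirm that the online baseline screen applies that threshold.

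The cost is one line of text under Suicidal intentions, a second in the eligibility section only if the range proves wrong, and a check of the baseline scoring rule.

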#### Problem solving skills

The 52-item Social Problem-Solving Inventory-Revised (SPSI-R; [52]) is used for measuring problem solving skills. Three of the five scales ((Positive problem Orientation (PPO; five items), Negative Problem Orientation (NPO; 10 items), and Avoidance Style (AS; seven items) showed to be sensitive for change [Warmerdam EH, van Straten A., Jongsma J, Twisk J, Cuijpers P: Online cognitive behavioral therapy and problem-solving therapy for depressive symptoms: Exploring mechanisms of change, submitted] and were therefore included in the study. Good internal consistency and test retest reliability are reported for all SPSI-R subscales within the manual [53].

#### Non-response

The Internet Intervention Adherence Measure [54] will be used to identify obstacles that interfered with the patient completing the program. Obstacles are categorized as Internet/computer/technical issues, personal/family issues, intervention-general issues, and intervention-specific issues. Patients are asked to respond to the 35 items on a 3-point scale from 1 to 3, indicating whether that obstacle had "no part," "a little part," or "a major part" in why they stopped using the program.

#### Other questions: demographic variables, time, currently under treatment

We will add demographic variables, location were participants rated the questionnaires, medication use and whether participants receive treatment by a mental health specialist.

For an overview of the instruments see Table 1.

**Table 1 T1:** Overview of questionnaires

		**Time of measurement**			
**Self rated questionnaires**	**Aim**	**T0** **Baseline (pre-test)**	**T1** **Post-test**	**T2** **Follow-up** **(3 months)**	**T3** **Follow-up (12 months)**
CES-D	Symptoms of depression	X	X	X	X
PHQ-9	Symptoms of depression	X	X	X	X
HADS	Symptoms of anxiety	X	X	X	X
BAI	Symptoms of anxiety	X	X	X	X
EuroQol	Quality of life	X	X	X	X
TIC-P	Health service uptake and production losses	X	-	X	X
Mastery scale	Mastery	X	X	X	X
CSQ-8 (condition 1–4)	Client satisfaction with treatment	-	X	-	-
WAI (condition 2–4)	Client satisfaction with coach	-	X	-	-
CEQ	Expectancy and treatment credibility	X	-	-	-
SQ	Motivation	X			
SAPAS	Personality disorder	X	-	-	-
WSQ	Common mental disorders	X	-	-	-
SPSI-R	Problem solving skills	X	X	X	X
Internet-Intervention Adherence Survey	Non-response, attrition	-	i.a.	i.a.	i.a.
Various	User characteristics	X	-	-	-

*i.a.: if applicable

### Sample size

The effects of the intervention on symptoms of depression and anxiety are the primary outcome measures and these are used as starting point for the power calculations. We assume that we want to be able to show differences between interventions and the control conditions with a standardized effect size (Cohen's *d*) of 0.35 [13]. Smaller effect sizes are considered to be not relevant from a clinical point of view. Assuming an alpha of 0.05 and a statistical power (1-Beta) of 0.80 in a one-tailed test, we need 100 respondents in each of the conditions. Overall, we need to recruit 500 respondents in total.

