Although the efficacy of internet-based self-help has been demonstrated sufficiently, it is not clear how these interventions should be offered to the population who can benefit from it. A major issue, for example, is whether it is better to offer the intervention with the support of a coach or if automated programs could work. In case support is necessary, it is not clear which level of support is needed. One of the advantages of a system without a coach is the ease and low costs of implementation, as it does not require a complex and costly structure of professionals. Furthermore, there is virtually no limit as to how many clients can enter the program, since additional clients will not imply additional therapist time [4]. On the other hand, a system organization, in which participants have to be assigned to coaches, will account for high costs and is more difficult to organize, since the coaches have to be trained, have to have sufficient time and have to be paid. There will also be limits on the amount of participants entering the program. However, legal and ethical issues of unguided programs (e.g., disappointment if the treatment fails, and the question of responsibility), the necessary risks of failing to identify cases for whom pure self-help is not enough, and the inability to monitor patients and adjust their treatment when necessary (e.g., in crisis situations) are arguments against unguided programs.

There is evidence that in interventions without a coach, compared to interventions with a coach, the drop-out rate is considerably higher [12]. Moreover, although interventions without a coach can be effective in reducing depressive and anxiety symptoms, they are associated with much smaller effect sizes than interventions in which the user had regular contact with a coach [12]. How large the differences in effectiveness are between interventions with and those without a coach has not been sufficiently studied. Moreover, it has not been examined whether there are differences in drop-out rate and costs between interventions with and without support, and in particular different levels of support. The aim of this study is to examine whether an internet-based self-help intervention with a coach is more effective than the same intervention without a coach in terms of clinical outcomes, drop-out and economic costs. Furthermore, this study examines which level of support by a coach is more effective compared to other levels of support.

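### The stated 80% power holds only for a one-tailed, complete-data comparison of intervention with control; there is no allowance for missing outcomes and no power for the coaching comparisons that are the trial's aims

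*Protocol article*

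**What the plan says.** The Sample size section of the protocol article powers the trial on "differences between interventions and the control conditions with a standardized effect size" of 0.35 (Cohen's d). It adds: "Smaller effect sizes are considered to be not relevant from a clinical point of view". It continues: "Assuming an alpha of 0.05 and a statistical power (1-Beta) of 0.80 in a one-tailed test, we need 100 respondents in each" of the conditions, and gives a recruitment total of 500, which is 5 × 100.

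The aims are stated in the Abstract, Background and Discussion. The first is whether the web-based intervention with a coach does better than the same intervention without one. The second is put this way in the Background: "this study examines which level of support by a coach is more effective compared to other levels of support". In the list under Study design, the first aim compares conditions 2 and 3 with condition 1. The second compares levels of support, most directly condition 2 (on demand) with condition 3 (weekly).

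The Statistical analysis section includes everyone randomized, imputes missing data by regression, and uses multiple regression with a treatment dummy. It states no sidedness. The Discussion foresees selective drop-out in the two control conditions and says missing values will be estimated.

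**The concern.** Three features of the calculation do not match the trial it supports.

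- **Missing outcomes.** The 100 per condition is the number needed for analysis, and it is also the number recruited. The article expects missing data but leaves no room for it.
- **Sidedness.** A one-tailed test needs a direction fixed in advance. The question of which level of support is better does not supply one.
- **Contrast.** The effect size is set for intervention versus control. The aims are comparisons among conditions that all receive the web-based intervention, and no effect size or power is given for them.

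The Discussion says the answer will bear heavily on how such interventions are disseminated. If a pairwise comparison of support levels is not significant, readers who believe it had 80% power may conclude that a coach is not needed, when a difference the article itself calls relevant could well have been missed.

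**Working it through.** **Inputs from the Sample size section:** d = 0.35 (SD 1), alpha 0.05, one-tailed, power 0.80, 100 per arm, five arms. **Assumptions of this check:** 0 to 30% of outcomes missing, equal across arms; two-sample t-test without covariates; only observed outcomes counted as information. Regression imputation keeps every randomized person in the data set, but an imputed value adds little or no new information on the treatment difference.

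**1. The plan's own figure.** Number per arm, normal approximation: n = 2 × [(z for alpha + z for power) / d]².

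- One-tailed: 2 × [(1.645 + 0.842) / 0.35]² = 100.9 (101.6 with the t distribution).
- Two-sided: 2 × [(1.960 + 0.842) / 0.35]² = 128.1, rounded up to 129 (129.1 with the t distribution).

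The stated 100 is therefore reproduced as a one-tailed, complete-data figure. The gap between 100 and 101 or 102 is rounding and is not a finding.

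**2. Power for one arm against another at d = 0.35.** Noncentrality = d × √(n/2). For n = 100 this is 0.35 × √50 = 2.475. The normal approximation gives one-tailed power Φ(2.475 − 1.645) = 0.797 and two-sided power Φ(2.475 − 1.960) = 0.697. The noncentral t gives:

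| Loss (assumed) | Analysed per arm | Noncentrality | One-tailed | Two-sided |
|---|---|---|---|---|
| 0% | 100 | 2.475 | 0.79 | 0.69 |
| 10% | 90 | 2.348 | 0.76 | 0.65 |
| 20% | 80 | 2.214 | 0.71 | 0.59 |
| 30% | 70 | 2.071 | 0.66 | 0.54 |

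All arms are the same size, so the table applies to any pair: intervention versus control, condition 2 or 3 versus condition 1, or condition 2 versus condition 3.

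**3. Detectable difference, two-sided, 80% power.** d ≈ (1.960 + 0.842) × √(2/n).

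- 100 per arm: 2.802 × 0.1414 = 0.396, about 0.40 (t: 0.398).
- 70 per arm: 2.802 × 0.1690 = 0.474 (t: 0.477, about 0.48).

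Both exceed the 0.35 that the article takes as the smallest relevant effect.

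**4. Conditions 2 and 3 together versus condition 1.** Noncentrality = d / √(1/n₁ + 1/n₂).

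- Complete data, 200 versus 100: 0.35 / √(1/200 + 1/100) = 2.858; two-sided power 0.81.
- 30% loss, 140 versus 70: 0.35 / √(1/140 + 1/70) = 2.391; two-sided power 0.66.

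**5. What a null pairwise result would show.** With 100 per arm, the 95% interval for a standardized difference has half-width of about 1.97 × √(2/100) = 0.28. An observed difference of 0.10 (illustrative) would have an interval of about −0.18 to 0.38, which still contains 0.35.

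**The case against.** **The first aim is directional.** The Background asks whether the coached version is more effective and cites smaller effects without a coach. A one-tailed test there can be criticized, but the article gives a basis for it. This stands: the case for two-sided testing is firm only for the support-level comparisons.

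**Changing the contrast does not in itself cost power.** At d = 0.35 coach versus no coach has the same power as any other pair of arms. This stands. A reader might infer that power for coach versus no coach, with drop-out, is 54 to 69%. The documents do not support that: 69% is two-sided with no drop-out at all, 54% needs an assumed 30% loss, and both require a two-sided test that the article does not specify for this aim. A smaller coaching effect would lower power (at an assumed d = 0.20, two-sided with complete data, 0.29), but the article gives no figure for that effect and regards anything below 0.35 as irrelevant.

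**Leaving the intervention is not the same as missing an outcome.** The Background remark on higher drop-out without a coach concerns the intervention, and everyone randomized is to be analysed. This stands too, so the point rests on the planned imputation and on the Discussion, which treats selective drop-out together with missing values.

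**Baseline adjustment could recover power.** All four primary scales are measured at baseline and the regression can take covariates. With an assumed baseline correlation of 0.5, the residual SD is √(1 − 0.25) = 0.866 and the effective d is 0.35 / 0.866 = 0.40, giving two-sided power of about 0.81 with complete data and 0.66 at 30% loss. This is a fair caveat, but the correlation is not in the article, and neither the Sample size section nor the analysis section commits to adjusting for baseline score.

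**Conclusion.** The concern holds in limited form. The arithmetic of the Sample size section is right for what it assumes; its assumptions do not fit the trial.

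- The stated 80% is a one-tailed, complete-data figure for intervention versus control. Recruiting exactly the number needed for analysis means that any loss takes power below it: about 0.76, 0.71 and 0.66 at assumed losses of 10%, 20% and 30% under the article's own test, unadjusted.
- For the non-directional comparison of support levels, two-sided power at d = 0.35 is about 0.69 with complete data and 0.54 at an assumed 30% loss. The chance of missing such a difference is thus about 31% to 46%.
- For coach versus no coach, the defect is that no effect size or power is stated. It is not that power is shown to be lower than for other pairs.

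The loss rates are assumptions, and baseline adjustment could offset part of the shortfall. The absence of any allowance for loss, and of any calculation for the main aim, does not depend on those assumptions.

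**What to change.** Keep 500 participants and restate the Sample size section with:

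1. an explicit assumption on missing outcomes, and the power that remains under it;
2. two-sided alpha 0.05, at least for the comparisons between support levels;
3. the power or detectable difference for coached versus uncoached (two-sided, 80% power: d of about 0.40 with 100 analysed per arm, 0.48 with 70);
4. if baseline adjustment is to be relied on, a commitment to it and the correlation assumed.

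Report the pairwise support-level comparisons as estimates with confidence intervals and read them against 0.35, so that a non-significant result is not taken as evidence that a coach is unnecessary.

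As an option, pre-specify conditions 2 and 3 together versus condition 1 as the test of the first aim (two-sided power 0.81 with complete data, about 0.66 at 30% loss). This averages on-demand and weekly support, the very distinction the second aim examines, so arm-specific estimates should stand beside it.

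The cost is a less favourable stated power. No participants or measurements are added.
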